### Assignment of interventions

After consenting to participation and completing screening assessments, eligible individuals will be randomly allocated, on a 1:1 ratio, to either ESGs + TAU or to TAU. The randomisation sequence will be generated by the Research Electronic Data Capture Service (REDCap) at the University of Bristol (https://brtcclinical.bris.ac.uk/redcap/). Randomisation will be stratified by centre. Appropriate staff at all sites, as delegated by the PI, will be provided with log-in details for the secure online randomisation system. Throughout the study, the randomisation list will be encrypted and held with the Trial Coordinating Office to ensure that the study researchers remain blinded to treatment allocation. At the end of the study, the randomisation list will be unencrypted and placed in the Trial Master File.

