#### Self-harming behaviour

Self-harming behaviour over the past week, will be measured using a single question: “Have you [in the past week] deliberately taken an overdose (e.g., of pills or other medication) or tried to harm yourself in some other way (such as cut yourself)?” [30]. Responses are rated 1—yes, once; 2—yes, more than once; or 3—no.

Arrangements for starting therapy will be discussed with those allocated to receive the intervention and these individuals will also be shown how to log onto the therapy platform. This discussion will take place during the baseline assessment if appropriate or, if necessary, a separate arrangement (for a later date) will be made with the participant to discuss therapy arrangements and login instructions.

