### Participant-centred outcome measures

As well as feasibility outcomes, data on participant-centred outcome measures proposed to be used in the main trial will also be collected. We will do this using a range of techniques according to participants’ preference including, online, telephone and paper questionnaires. This will allow exploration as to which techniques for data collection are most acceptable and feasible.

The timing and sequence of all assessments are summarised in the SPIRIT figure (Fig. 4). All study participants will complete follow-up assessments at 2 and 4 months post-randomisation. At the 4-month data collection point, all the outcomes that were assessed at baseline will be reassessed. In addition, at 4-month follow-up, resource use will be collated by maternal self-report.

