### Blinding

It will not be possible to blind participants or the treating clinicians to the participant’s treatment allocation because of the nature of the intervention. The statistician and health economist will be blind to the trial condition throughout the feasibility trial. The Trial Manager and research assistants will not be blind to the group as they will also be responsible for participant recruitment and reminder telephone calls for completion of follow-up data.

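### The protocol says the study researchers stay blinded and also that the trial manager and research assistants are not, and its randomisation trigger does not require baseline questionnaires to be finished first

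*Protocol article*

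**What the plan says.** **Who is blind.** Assignment of interventions says that, for the duration of the study, the encrypted randomisation list is kept by the coordinating office to "ensure that the study researchers remain blinded to treatment allocation". The next section, Blinding, says: "The Trial Manager and research assistants will not be blind to the group as they will also be responsible for participant recruitment", and adds reminder calls for follow-up data to their duties. On who is blind, it says: "The statistician and health economist will be blind to the trial condition throughout the feasibility trial". Participants and treating clinicians cannot be blinded.

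**When randomisation happens.** Assignment of interventions reads: "After consenting to participation and completing screening assessments, eligible individuals will be randomly allocated". The Methods part of the Abstract gives the same trigger. The sections on screening and on baseline assessment place written consent before the baseline assessment begins.

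**When allocation is discussed.** The paragraph that closes the baseline section (printed under Self-harming behaviour) deals with arrangements for starting therapy with women already allocated to the groups. It says: "This discussion will take place during the baseline assessment if appropriate". Otherwise a later date is arranged.

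**What points the other way.** The Abstract and the Data analysis section both list, as a single feasibility proportion, participants who complete baseline measures and are randomised, with baseline named first.

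**The concern.** There are two linked faults in how the protocol fixes knowledge of allocation.

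The first is the blinding statement. A reader of Assignment of interventions would conclude that the people who deal with participants do not know the allocation. A reader of Blinding would conclude that they do. Whichever sentence is carried into the trial report or the definitive protocol decides how the risk of bias is judged, and the claim of blinded researchers would be wrong.

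The second is the order of baseline and allocation. Apart from the sociodemographic items, the baseline battery is self-report: borderline symptoms, distress, quality of life, wellbeing, social functioning, parenting stress and self-harm in the past week. A woman who has just learned that she will, or will not, be offered the groups may answer differently, and in a different direction by arm. Scores given after that moment no longer describe the two groups before allocation. Completeness of baseline data is itself a feasibility outcome, and it too could then depend on allocation. Producing a protocol for a definitive trial is a stated objective, so an unclear sequence here could be passed on to a trial where it matters more.

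**Working it through.** No arithmetic applies. No alpha, power, effect size or standard deviation bears on the point, so the check is to set the statements side by side.

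**Step 1: can both blinding statements be true?**
- Assignment of interventions: the study researchers remain blinded to allocation throughout.
- Blinding: the trial manager and research assistants are not blind, because they recruit and make the reminder calls.
- In the sections on screening and baseline, the word researcher is used for the person who contacts potential participants, screens them, takes consent and supports the questionnaires.
- Blinding gives recruitment to the trial manager and research assistants, so the two statements appear to describe the same people.
- Assignment of interventions also gives delegated site staff log-ins to the online randomisation system.

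The statements could be reconciled only if study researchers meant the statistician and health economist alone. The article nowhere defines the term that way, and its ordinary use of the word runs against it. The two sections conflict.

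**Step 2: when does the stated trigger for randomisation become satisfied?**
1. Screening is completed and the woman is found eligible.
2. Written consent is taken before the baseline assessment starts.
3. At that point both named conditions, consent and screening, are met.
4. The baseline assessment, of about one hour, comes next.

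Taken literally, the trigger is met before any baseline questionnaire has been opened.

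**Step 3: does any other text close the gap?**
- The therapy discussion is held with women already allocated and may take place during the baseline assessment. In those cases allocation exists, and is known to the woman and the researcher, within that appointment.
- Two sequences fit this. In (a), all questionnaires are submitted, then the woman is randomised, then therapy is discussed. In (b), the woman is randomised and told while some or all questionnaires are outstanding.
- The feasibility proportion that names baseline before randomisation favours (a). So does the position of the therapy paragraph, after all the questionnaires have been described.
- Neither is a rule. The first is the label of an outcome, and the second is the order of the text. The section that governs assignment does not name the step.

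**Result.** The blinding statements contradict each other. Sequence (b) is permitted by the text, although (a) is probably what was intended.

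**The case against.** The strongest reply is that both matters are loose wording. Blinding is the dedicated section, goes role by role and gives its reason. The sentence in Assignment of interventions concerns custody of an encrypted list and may be allocation concealment described as blinding. That is a likely explanation, but the sentence says that researchers remain blinded for the whole study, so it still needs correcting.

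On sequence, the reply is that baseline is clearly meant to come first, that the therapy discussion naturally falls at the end of the appointment or on a later date, and that the flow chart and SPIRIT figure, which may settle the order, are not shown. Much of this stands. It shows that the problem is an incomplete trigger, not a plan to randomise before baseline. It does not supply the missing condition.

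The reply on consequences also carries weight. This is a feasibility trial. Its progression criteria are recruitment, uptake of the groups and follow-up completion, none of which uses baseline scores. The Data analysis section plans differences in means with confidence intervals, without hypothesis tests, and mentions no baseline adjustment.

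Some stronger readings are tempting and are not supported:
- **Telephone interviewer bias.** Outcomes may be collected by several modes, "including, online, telephone and paper questionnaires", and unblinded staff make reminder calls. A reader might infer that unblinded staff also conduct telephone assessments. The article does not say who does, and a reminder call is not an outcome interview.
- **A stated amount of bias, or all 48 baselines affected.** Nothing in the documents gives the share of baselines completed after disclosure, or the shift in scores that would follow.
- **Bias in a baseline-adjusted comparison.** No such analysis is stated.

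**Conclusion.** The point holds in two parts of different strength. The contradiction on researcher blinding is certain on the face of the protocol; it rests only on reading researcher as the article itself uses the word. The sequencing gap is well supported as something the text permits: the trigger omits baseline completion, consent precedes baseline, and allocation may be discussed within the baseline appointment. It is not shown that any woman will complete baseline after learning her allocation, and the missing figures may state the intended order.

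No numerical size can be given. The effect on the feasibility conclusions is probably small. Participants cannot be blinded and outcomes are self-reported, so most reporting bias after baseline is unavoidable; what can be avoided cheaply is baseline reporting after disclosure. That the research assistants are unblinded is a declared design choice and is not faulted here. The corrections should be made because they cost almost nothing and because these procedures may be carried into a definitive trial.

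**What to change.** 1. In Assignment of interventions, replace the claim that study researchers stay blinded. Say that the encrypted list conceals upcoming allocations until each woman is randomised, and that only the statistician and health economist are blinded, in agreement with the Blinding section.
2. In the same section and in the Abstract, change the trigger to: after consent, screening and submission of all baseline questionnaires. Enforce it in REDCap, so that the randomisation function opens only when the baseline forms are submitted.
3. In the therapy-arrangements paragraph, state that allocation and arrangements are discussed only after that point, whether later in the same appointment or on another date.

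The cost is three wording changes and one rule in the randomisation system, with slightly less scheduling flexibility, because a woman who cannot finish the questionnaires in one sitting would be randomised later. The choice of follow-up modes by participant preference need not change; exploring which modes work is one of the trial's purposes.

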### Blinding

It will not be possible to blind participants or the treating clinicians to the participant’s treatment allocation because of the nature of the intervention. The statistician and health economist will be blind to the trial condition throughout the feasibility trial. The Trial Manager and research assistants will not be blind to the group as they will also be responsible for participant recruitment and reminder telephone calls for completion of follow-up data.

### Adverse events

All adverse events will be assessed for seriousness, causality and expectedness by the Principal Investigator and will be recorded and reported from the point of randomisation until the 4-month follow-up assessment or the point of withdrawal from the study. Hospitalisations for elective treatment of a pre-existing condition will not be reported as serious adverse events.

### Data management

A web based electronic Case Report Forms system will be used to collect baseline and outcome data. Study data will be archived securely and destroyed after 10 years. No data analysis will be undertaken until databases are locked.

Trial staff will ensure that the participants’ anonymity is maintained through protective and secure handling and storage of patient information at the trial centres. Each study participant will be assigned a unique participant identification number at the start of the assessment process. This number will be written on all assessment forms, contemporaneous notes and the database used to record data on study participants.

All documents will be stored securely and made accessible only to trial staff and authorised personnel. A hard copy of a record sheet linking patient identity and the randomisation code for all participants will be kept at each site along with the Participant Contact Details Form. Both will be placed in the Investigator Site File, in a locked filing cabinet, separate from the paper CRFs and other documents (e.g. contemporaneous notes) relating to a participant, which will be anonymised. Once the study is over, the site investigator will arrange the long-term storage (archiving) of all research data which will include the record sheet linking patient identity.

An electronic copy of participants’ contact details will be stored on a secure drive. At the end of the study, the electronic record sheet and the hard copy of the Participant Contact Details will be destroyed once interested participants have received a copy of the study results. Hard copies of trial allocation letters that are sent to participants and clinical teams will be stored in the Trial Master File and archived as evidence of the detailed trial procedures. Data from screening, baseline and follow-up assessments will be stored on a secure database and access will be restricted to members of the research team. Audio recordings and interview transcripts will be stored securely on a password protected server at the university co-ordinating centre. The contact details of therapists delivering the study intervention will be kept on an encrypted file at University of Bristol and will be deleted at the end of the study.

### Data analysis

Data will be analysed and reported following the CONSORT guidance extension to feasibility studies [35], including a CONSORT flow diagram and focussing principally on descriptive statistics of key feasibility parameters. We will assess the feasibility and acceptability of the trial design by calculating proportion (and 95% CIs) of participants: (1) consenting; (2) completing baseline measures and randomised; (3) completing the intervention—i.e. attending at least nine out of 12 sessions (75%) (4) completing follow-up assessments. Descriptive statistics for patient characteristics and outcomes will be reported overall and by treatment group; as means or medians with measures of dispersion for continuous data (as appropriate given the form of their distribution) and frequencies and percentages for categorical data. For participant outcomes, the proportion with complete data, for each outcome, will be reported in addition to descriptive statistics. The effect of treatment on outcomes will be estimated on an intention-to-treat basis and reported as difference in means between groups and associated confidence intervals only, since the study has not been powered for formal statistical hypothesis testing.

Data from the nested qualitative study will be analysed thematically using NVivo [36] to aid data management. The interview transcripts will be individually read and re-read, from which an initial coding framework will be developed. Independent double coding of a subgroup of transcripts will take place. Team members will meet to discuss the developing coding framework, to ensure that the emerging analysis is trustworthy and credible. This framework will be refined, with coded material regrouped, as new data from subsequent interviews are gathered and a deeper level of understanding is achieved. Descriptive accounts will be produced of main themes and constant comparison will be used to explore similarities and differences across groups of participants.

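### The difference-in-means rule, read as written, also covers the self-harm item, whose codes cannot be averaged; the sentence should be limited to continuous outcomes and should name baseline and centre adjustment

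*Protocol article*

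**What the plan says.** The effect of treatment is covered by one sentence in the Data analysis section. Its subject is outcomes without qualification: "The effect of treatment on outcomes will be estimated on an intention-to-treat basis". The result is to be "reported as difference in means between groups and associated confidence intervals only", and the reason given is "since the study has not been powered for formal statistical hypothesis testing".

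Earlier in the same paragraph, the descriptive statistics, overall and by treatment group, are split by type of data: means or medians with dispersion for continuous variables, and "frequencies and percentages for categorical data". The effect sentence does not repeat that split.

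Self-harm is one of the baseline measures. Under Self-harming behaviour the coding is given: "Responses are rated 1—yes, once; 2—yes, more than once; or 3—no". Under Participant-centred outcome measures, at 4 months "all the outcomes that were assessed at baseline will be reassessed", so self-harm is an outcome to which the effect sentence applies. Resource use is added at 4 months only.

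On the design, Assignment of interventions states that women are "randomly allocated, on a 1:1 ratio, to either ESGs + TAU or to TAU" and that "Randomisation will be stratified by centre". The effect sentence mentions neither baseline values nor centre.

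**The concern.** There are two separate matters.

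The first is an error in the rule as worded. A difference in means needs a variable whose numerical values carry order and distance. The self-harm codes carry neither: the most severe response sits in the middle and the absence of self-harm has the highest code. Applied literally, the rule gives an estimate and interval that can show no difference where one arm is clearly worse, or can favour the worse arm. The Background lists self-harm among the common problems of women with this diagnosis, and the measures are the ones proposed for the main trial, so a misleading contrast on this item would be carried forward.

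The second is a gain left unclaimed. The trial already collects a baseline value for nearly every outcome and stratifies by centre. If the mean differences are taken as simple contrasts, their confidence intervals will be wider than the same data allow.

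**Working it through.** The article gives no precision or power figure for the treatment effect, so there is none to reproduce. The one interval under Sample size concerns the recruitment proportion and does not bear on this point.

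**Self-harm item**

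Inputs: codes 1 (once), 2 (more than once) and 3 (no), from Self-harming behaviour; 24 women per arm, from the target of 48 at 1:1. The counts below are illustrations, not data.

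Mean code = (1 × n₁ + 2 × n₂ + 3 × n₃) / n.

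- All women more than once: mean 2.0. Half once and half no: (1 + 3)/2 = 2.0. The difference is 0.
- Arm A with 6 once, 0 more than once, 18 no: (6 + 0 + 54)/24 = 2.50, with 6/24 = 25% self-harming. Arm B with 0 once, 12 more than once, 12 no: (0 + 24 + 36)/24 = 2.50, with 12/24 = 50% self-harming, all repeatedly. The difference in means is 0, although the proportion doubles.
- With 8 of 24 self-harming in each arm: if all did so once, (8 + 48)/24 = 2.33; if all did so more than once, (16 + 48)/24 = 2.67. The arm with repeated self-harm scores closer to the code for no.

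For arms A and B, the difference in proportions is 50% − 25% = 25 percentage points. Its standard error is √(0.25 × 0.75/24 + 0.50 × 0.50/24) = 0.135, so a simple 95% half-width is 1.96 × 0.135 = 0.26. That is imprecise, as expected at this size, but it is interpretable.

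**Adjustment for baseline and centre**

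Inputs: 36 women followed up, which is 75% of 48 (Progression criteria), taken as 18 per arm; the full 48 for comparison; two centres. The baseline-to-follow-up correlation r is not in the document and is assumed to lie between 0.3 and 0.7. Centre is assumed to explain no variance and to cost one degree of freedom.

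Unadjusted 95% half-width in SD units = t(0.975, n − 2) × √(4/n).
Adjusted half-width = t(0.975, n − 4) × √(4/n) × √(1 − r²).

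| | n = 36 | n = 48 |
|---|---|---|
| Unadjusted | 0.68 | 0.58 |
| Adjusted, r = 0.3 | 0.65 | 0.56 |
| Adjusted, r = 0.5 | 0.59 | 0.50 |
| Adjusted, r = 0.7 | 0.48 | 0.42 |

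At either sample size the interval is about 4%, 13% or 28% narrower at r = 0.3, 0.5 or 0.7.

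**The case against.** **On self-harm.** The article nowhere says that the codes will be averaged; they may be no more than response labels. The same paragraph gives categorical data frequencies and percentages by treatment group, and the contrasts shown above would be plain in such a table. A sensible analyst would confine mean differences to the scale scores. The item is also one of several in a feasibility study. Most of this stands: the information would not be lost. But it does not rescue the effect sentence, which covers outcomes without exception and names no effect measure for a categorical one. The split made for the descriptive statistics shows that the distinction was available and was not carried over.

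**On adjustment.** A reader might infer that the article fixes raw differences and so discards the baseline values and the strata. The text does not support that. It says neither raw nor unadjusted. The word 'only' is explained by the clause that follows it, which rules out hypothesis tests, not covariates. A baseline- and centre-adjusted difference is still a difference in means. Covariates are commonly left to the analysis plan, which is not shown, so silence about them is not an error. This objection stands in full.

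**On consequences.** A reader might also infer that chance baseline imbalance would bias the result, that the intervals are the only effect information passed on, or that the residual SD needed to plan the main trial could not be obtained. None of these follows. Under 1:1 randomisation the unadjusted estimate is unbiased. Outcomes are also summarised by arm. Baseline and 4-month data are both collected, so the residual SD can be computed. Finally, the choice to adjust, and the choice to dichotomise self-harm (which merges once with more than once), are partly matters of preference. That is fair, and it is why the three-category table should be kept.

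**Conclusion.** The point holds in two parts of different weight.

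The stated rule is wrong for the self-harm item. This follows from the coding and the wording alone and needs no assumption beyond reading the sentence literally. The error is confined to one item and the descriptive table limits the damage, but the effect estimate that the sentence calls for would be uninterpretable.

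Naming the adjustment is an improvement, not the correction of a bias or of a stated error. Its size depends on a correlation that the document does not give: about 4% narrower intervals at 0.3, rising to about 28% at 0.7. It applies only to continuous outcomes that have a baseline value.

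Neither part touches the decision to proceed. The progression criteria rest on recruitment, uptake and completion of follow-up, and none of them uses a treatment effect.

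**What to change.** Reword the effect sentence in the Data analysis section, or settle it in the analysis plan before the database is locked, along these lines:

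*For continuous outcomes measured at baseline, the intention-to-treat effect is the difference in means with 95% CI from a linear model with treatment group, the baseline value of the outcome and centre. For self-harm, the effect is the difference between groups in the proportion reporting any self-harm in the past week (codes 1 or 2 versus code 3) with 95% CI, and the frequencies of all three responses are shown by group. No hypothesis tests are made.*

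Continuous measures without a baseline value, such as those derived from resource use, would be adjusted for centre only. Reporting the observed baseline-to-follow-up correlation and the residual SD for each scale would also help in sizing the definitive trial.

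The cost is a change of wording. It needs no new data, no extra assessments and no change to the sample size or the progression criteria.
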